### 2.2 Randomization

Once the participants are enrolled, they will be allocated a unique identification number according to their screening order. Participants will be distributed into four treatment groups in a 1:1:1:1 ratio through computerized randomization. A web administrator will independently enter the randomization list, containing consecutive drug numbers, into a blinded datasheet. The numbers will be randomly allocated to participants of the intervention groups or the control group with an opaque, sealed envelope by a third person unaware of the assignments to study groups.

### 2.3 Interventions

All participants who sign the informed consent will first enter a 1-month washout period during which insulin is used as basal therapy to avoid interference of previous hypoglycemic therapy on the study results. The proportion of patients treated with insulin will be comparable in each group. According to the individual characteristics of each subject, the investigator and the physician in charge should determine the brand, dosage form, initial injection dose and frequency of insulin. The optimal glycemic control target is fasting blood glucose (FBG) in the morning <7.2 mmol/L and 2 hours postprandial blood glucose (PBG)<10.0 mmol/L. The dose and dosage form of insulin will be adjusted or switched based on the subjects’ average blood glucose level over the three days preceding each visit. Other antidiabetic drugs will be prohibited throughout the study. After completing the screening and evaluation, the research nurses will implant the dynamic blood glucose monitor subcutaneously for the participants and advise them on the appropriate nursing measures. Prior to the intervention, participants will receive a 1-week diabetes health education as well as a baseline assessment. Then, they will be randomly divided into the following four groups: BBR (0.6 g per 6 pills, twice daily before meals) plus inulin (0.6 g per 6 pills, twice daily before meals), BBR plus placebo (inulin), inulin plus placebo (BBR), or placebo (inulin) plus placebo (BBR). BBR is manufactured by Yabang Epson Pharmaceutical Co., Ltd., Yancheng, Jiangsu, China. Inulin was purchased from Sino Peptide Health Technology Co., Ltd., Beijing, China, and its raw material supplier was Cosucra in Belgium. If desired, inulin can be processed into different dosage forms. The placebos are similar in appearance to BBR and inulin. Each type of tablet is packaged uniformly in an opaque sealed bottle with instructions and labels. The care providers and participants will be blinded to the assignment of medicine. After 3 months of treatment, participants will be asked to return the drug packages to determine their compliance. Researchers will conduct regular follow-up by telephone with all the participants to encourage and improve medication compliance, and record related adverse events including hypoglycemia and gastrointestinal symptoms.

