**Methods and Analysis:**

We will conduct a single-center, prospective, randomized, double-blind, placebo-controlled trial. A total of 240 patients with LADA who have started insulin therapy will be randomly allocated either to the intervention or control group. After a 1-week run-in period, they will complete a 3-month treatment of BBR alone, inulin plus BBR, inulin alone, or placebo. Anthropometric and clinical data will be collected at five time points: baseline, 3 months, 6 months, 9 months, and 12 months from baseline. The primary outcome was the change in glycated hemoglobin levels. Dynamic blood glucose parameters, β-cell function, and gut microbiota, as well as adverse events and quality of life will be monitored.

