In animal experiments, it has been shown that compared with BBR alone, BBR combined with prebiotics has been shown to continuously reduce FBG, improve glucose tolerance, and ameliorate the balance of α- and β-cells in diabetic db/db mice (25). Similarly, Cao et al. found that the combination of BBR and prebiotics in the intervention of KKAy mice was more effective than BBR alone in blood sugar control, improvement of insulin resistance and pancreatic β-cell function, reduction of inflammatory mediators, and maintenance of intestinal barrier integrity (26). These findings suggest that the combination of BBR and prebiotics may be a novel pharmaceutical strategy for diabetes. Hence, the present study aims to evaluate the effectiveness of combining BBR and inulin on diabetes care, particularly glycemic control in patients with LADA. We will also evaluate the safety and tolerability of the combined drugs.

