### 2.4 Outcome Assessment

#### 2.4.1 Primary and Secondary Outcomes

The primary outcome measure is the change in mean HbA1c level, measured at baseline and 3 months post-intervention, which reflects the blood glucose management status of the participants.

The secondary outcome measures include: (1) the frequency of hypoglycemic events and drug-related side effects; (2) the change in C-peptide for assessing β-cell function and the incidence of acute and chronic diabetes complications; (3) daily insulin dose and medical service utilization, such as diabetes-related hospital admissions and emergency visit rate; (4) the alteration of gut microbiota assessed by multiomics measurements and the differences in intestinal permeability; and (5) the quality of life assessed by the Audit of Diabetes Dependent Quality of Life (ADDQoL-19) containing physical functioning, symptoms, psychological well-being, social well-being, role activities and personal constructs with its Chinese version CN-ADDQoL also having the individualized properties, satisfactory reliability and validity (Cronbach’s alpha=0.941) (26).

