#### 2.4.3 Data Collection

After the screening, all qualified participants with LADA will enter a 1-month washout period. After the stable control of diabetes with insulin, all enrolled participants will complete the baseline survey for a period of 1 week. The primary endpoint results will be collected after 3 months of intervention. Then, participants will receive outpatient visits every 3 months until the end of the study. The research assistants involved in data collection and evaluation will not be informed of the grouping of participants. The evaluation and data collection process is shown in **Table 1**. The participants will record their daily dose of medications, abnormal self-monitoring of blood glucose levels, combined medications and adverse events. Before each visit, participants will be asked to fill out an online survey of nutritional status in the past week to assess calorie intake, including the content of carbohydrates, fat, protein and fiber in the diet. Nurses will instruct patients to record the type and quantity of daily food *via* online and mobile platforms. In addition, it is worth noting that participants should not consume fermented dairy products (such as yogurt) or probiotics 7 days before the visit and should avoid high-fat diets 3 days before the visit.

**Table 1 T1:** Patient flow of enrolment, intervention and outcome measurements.

		PS	M0	M3	M6	M9	M12
**Enrolment**	Recruitment	×					
	Eligibility Screening	×					
	Informed consent	×					
	Allocation		×				
**Intervention**	Insulin injection	•					•
	Experimental drugs / placebo		•	•			
**Outcomes**	Demographic characteristics (Age, sex, nationality, occupation, marital status, residence and education level)		×				
	Anthropometric variables (BMI, waist and hip circumference, heart rate and blood pressure)	•					•
	Insulin logs		•				•
	Dietary logs		•				•
	CGMS*		•				•
	Metabolic parameters (HbA1C, FBG, PBG, FCP, 2hCP, Triglyceride, Total cholesterol, HDL cholesterol, LDL cholesterol)	•					•
	HOMA-IR**		•				•
	Insulin autoantibody (GADA, IA2A, ZnT8)	×	×	×			×
	Serum inflammation markers		×	×			
	Chronic complication screening (Carotid ultrasound, UCG, fundus examination, urinary albumin-creatinine ratio, eGFR)		×				×
	Gut microbiota (Metagenomics, stool metabolomics, plasma metabolomics)		×	×			×
	Intestinal permeability		×	×			×
	Drug safety assessment (Blood routine, Liver and kidney function testing, Serum electrolytes, Blood ketones, electrocardiogram)		×	×			

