	Quality of Life Questionnaire***		×	×			×
	Adverse events record (hypoglycemic events and drug-related side effects)		×	×			

PS, prior to study; M0, baseline assessment; M3, 3 months from the baseline; M6, 6 months from the baseline; M9, 9 months from the baseline; M12, 12 months from the baseline. *CGMS, continuous glucose monitoring system; **HOMA-IR, homoeostasis model assessment index for assessing insulin resistance; ***questionnaire: CN-ADDQoL.

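### Apart from hypoglycemia, the clinical adverse-event outcome counts only events judged drug-related, while other parts of the protocol refer to adverse events without that condition

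*Protocol article*

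**What the plan says.** The protocol article describes clinical adverse events in two ways.

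**With a relatedness condition**
- Section 2.3 (Interventions), telephone follow-up: researchers will "record related adverse events including hypoglycemia and gastrointestinal symptoms".
- Section 2.4.1, secondary outcome 1: "the frequency of hypoglycemic events and drug-related side effects".
- Table 1 in Section 2.4.3, the adverse-event row: "Adverse events record (hypoglycemic events and drug-related side effects".

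**Without one**
- Abstract, Methods and Analysis: "as well as adverse events and quality of life will be monitored".
- Section 2.4.3, participant records: "abnormal self-monitoring of blood glucose levels, combined medications and adverse events".

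The Introduction sets the aim: "We will also evaluate the safety and tolerability of the combined drugs". Some safety data need no attribution. Table 1 lists "Drug safety assessment (Blood routine, Liver and kidney function testing, Serum electrolytes, Blood ketones, electrocardiogram", and Section 2.4.1 includes diabetes complications, admissions and emergency visits as outcomes. On blinding, Section 2.3 says "The care providers and participants will be blinded to the assignment of medicine", and Section 2.4.3 extends this to the research assistants who collect and evaluate data.

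**The concern.** In a randomized, placebo-controlled trial, comparing all events by arm shows what the treatment causes without anyone judging individual cases. An outcome that first requires an event to be judged drug-related gives up that advantage. An unexpected effect is the kind least likely to be attributed to the study product, so it is the kind most likely to drop out.

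The events exposed to this filter are clinical adverse events other than hypoglycemia. They include gastrointestinal symptoms, which Section 2.3 itself singles out and which matter for the tolerability of oral products. The article does not say who judges relatedness. Nor does it say which drug is meant, although all participants also receive insulin. At stake is the answer to the safety and tolerability aim. The HbA1c outcome and its sample size are not affected.

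**Working it through.** The article gives no adverse-event rate, safety hypothesis or safety power, so there is no stated figure to reproduce. The check is mainly a comparison of the texts, followed by a short illustration.

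**1. What enters the arm comparison under the outcome as written**

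| Type of event or measurement | Needs a relatedness judgement? | Source |
|---|---|---|
| Hypoglycemic events | No | Section 2.4.1, Table 1 |
| Laboratory tests and ECG | No | Table 1 |
| Diabetes complications, admissions, emergency visits | No | Section 2.4.1 |
| Gastrointestinal symptoms | Yes | Section 2.4.1, Table 1 |
| Any other clinical adverse event | Yes | Section 2.4.1, Table 1 |

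The diary is a source of data. Section 2.4.1 and Table 1 define what is counted, and no section defines an all-cause adverse-event outcome.

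**2. Dilution when attribution is equal in all arms**

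Input from the protocol: n = 60 enrolled per arm (Section 2.1.2). Assumed: true event proportions pC = 0.10 and pT = 0.30, and a share s of events judged related, the same in both arms. Then:

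- observed proportion = s × p
- observed difference = s × (pT − pC)
- power at two-sided 0.05 = Φ{[Δ − 1.96·√(2·p̄(1−p̄)/n)] / √([pC(1−pC) + pT(1−pT)]/n)}, with the observed proportions put in, Δ their difference and p̄ their mean

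| s | Observed proportions | Difference | Power |
|---|---|---|---|
| 1.0 | 10% vs 30% | 20 points | 79% |
| 0.8 | 8% vs 24% | 16 points | 67% |
| 0.6 | 6% vs 18% | 12 points | 53% |
| 0.4 | 4% vs 12% | 8 points | 36% |

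For s = 0.6: √(2 × 0.12 × 0.88/60) = 0.0593 and √((0.0564 + 0.1476)/60) = 0.0583. So (0.12 − 1.96 × 0.0593)/0.0583 ≈ 0.06, and Φ ≈ 0.53.

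**3. The opposite effect: background events**

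Counting all events also brings in events unrelated to treatment. With an independent background proportion b in both arms, each proportion becomes 1 − (1 − p)(1 − b). For an assumed b = 0.20:

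- 1 − 0.90 × 0.80 = 28%, against 1 − 0.70 × 0.80 = 44%
- difference 16 points, power 45%

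That is below the 53% for 60% attribution in the table above, which assumes that no background event is labelled related. Neither count is always the more powerful.

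**4. What distortion would require**

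A false difference appears only if attribution differs between arms. With equal true rates of 30% and attribution of 40% against 60%, the observed proportions are 0.30 × 0.40 = 12% and 0.30 × 0.60 = 18%, a spurious 6 points. Nothing in the documents shows such an imbalance.

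**The case against.** A reader might infer that safety is defined by related events only, that staff guesses about allocation decide what counts, and that the comparison is therefore distorted and loses a known amount of power. The documents do not support this stronger reading, for four reasons.

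- **Only related events.** This is wrong. Hypoglycemia stands beside the drug-related term in Section 2.4.1 and Table 1 without a condition of its own. Laboratory tests, ECG, complications and admissions are collected whatever the cause.
- **Staff guesses and distortion.** No section says who judges relatedness. Participants, care providers and data collectors are blinded and the placebos look similar, so attribution error should be about equal across arms. Distortion would need unequal attribution, for example if tolerability revealed the allocation, and that is not shown.
- **Loss of power.** Every rate in the illustration is assumed, and background events can reverse the ranking.
- **The wording in Section 2.3.** There, related may simply mean relevant. The sentence lists types of event and sets no formal causality rule.

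These points stand, and they narrow the concern. It can also be argued that all events are collected and that causality grading is left to a fuller document. That would excuse silence. Here, however, Section 2.4.1 and Table 1 give a restrictive definition, which differs from the abstract and the diary. Blinding equalizes attribution error between arms but does not bring back events that were left out.

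**Conclusion.** The point holds as a defect in a stated outcome definition together with an internal inconsistency. It rests mainly on Section 2.4.1 and Table 1; the looser phrase in Section 2.3 is only supporting evidence. For clinical events other than hypoglycemia, following the plan as written omits whatever is not judged drug-related.

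Under the stated blinding, the expected consequences are missed unexpected effects and an absolute difference reduced by the factor s. Because neither s nor any event rate is given, the size cannot be fixed: under the assumed rates above, a 20-point difference would shrink to between 16 and 8 points for s from 0.8 to 0.4. The case for an all-cause count is that it removes selection by judgement. It does not rest on a promised gain in power. This is a cheap and worthwhile improvement to a secondary outcome.

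**What to change.** Define secondary outcome 1 as all adverse events of any cause, serious adverse events and hypoglycemic events, compared by randomized arm. Record relatedness for each event, graded blind to allocation by a named role, and report the events judged related as a subset beside the all-cause count. Then bring Section 2.3, Section 2.4.1 and the adverse-event row of Table 1 into line with the abstract and the participant records in Section 2.4.3.

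The cost is a change of wording and slightly more data entry, with no new visits. The downside is some background noise in the all-cause count, which reporting the related subset alongside addresses.

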### 2.4 Outcome Assessment

#### 2.4.1 Primary and Secondary Outcomes

The primary outcome measure is the change in mean HbA1c level, measured at baseline and 3 months post-intervention, which reflects the blood glucose management status of the participants.

The secondary outcome measures include: (1) the frequency of hypoglycemic events and drug-related side effects; (2) the change in C-peptide for assessing β-cell function and the incidence of acute and chronic diabetes complications; (3) daily insulin dose and medical service utilization, such as diabetes-related hospital admissions and emergency visit rate; (4) the alteration of gut microbiota assessed by multiomics measurements and the differences in intestinal permeability; and (5) the quality of life assessed by the Audit of Diabetes Dependent Quality of Life (ADDQoL-19) containing physical functioning, symptoms, psychological well-being, social well-being, role activities and personal constructs with its Chinese version CN-ADDQoL also having the individualized properties, satisfactory reliability and validity (Cronbach’s alpha=0.941) (26).

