However, a portion of LADA cases can often be misdiagnosed as T2D, with misdiagnosis rates ranging from 5% to 10% in various studies (9). Moreover, misdiagnosed LADA cases are usually treated with therapies commonly used in T2D, which might contribute to the progression of diabetes toward insulin dependence and threaten the health and life of patients (10). Since LADA individuals generally have some residual β-cell function, LADA treatment should aim to achieve good metabolic control while also retaining residual insulin secretion capacity (11). Currently, insulin is the most commonly used therapeutic option for LADA patients. Several randomized clinical trials have found that regardless of the initial C-peptide level and residual β-cell function, clinicians tend to prescribe insulin treatment for LADA patients at an early stage (12). However, whether insulin is truly appropriate as the initial treatment for LADA patients is still debatable. Although LADA patients have better metabolic parameters at baseline than T1D and T2D patients (13), evidence suggests that there is almost no difference in the prognosis of complications and risk of death among the three groups (14–16). Given that insulin alone may not be sufficient to control blood glycemic levels, combination therapy may have the potential to improve long-term blood glucose control and delay disease progression in LADA patients. Because there have been few clinical studies on LADA, more large-scale clinical trials are needed to explore the optimal treatment of LADA.

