## 2 Methods

### 2.1 Trial Design

This is a prospective, randomized, double-blinded, placebo-controlled trial with a 1-month washout period, a 1-week run-in period, a 3-month treatment period, and a 9-month follow-up period. The participants will be arranged to enter a 1-month washout period after obtaining their informed consent during which basic treatment medications are adjusted, and then they will be allocated to enter a 1-week run-in period for lifestyle education and collection of baseline data and samples. After the run-in period, they will be randomized 1:1:1:1 to one of four groups: BBR-alone, inulin plus BBR, inulin-alone, or placebo. This study will use a stratified random method to balance the following factors: BMI ≥25 kg/m^2^ and <25 kg/m^2^, with or without chronic complications of diabetes. Measurements will be implemented at baseline prior to the intervention and at 3 months, 6 months, 9 months and 12 months from baseline. The research flowchart is shown in **Figure 1**.

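### HbA1c is scheduled to M12 through nine months off drug, but the article names it as an outcome only at M3 and gives it one undated ANOVA without baseline

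*Protocol article*

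**What the plan says.** - **Periods.** Section 2.1 describes "a 3-month treatment period, and a 9-month follow-up period". In Table 1 the row "Experimental drugs / placebo" is marked at M0 and M3 only, so M6, M9 and M12 are off drug.
- **Visits.** Section 2.1: "Measurements will be implemented at baseline prior to the intervention and at 3 months, 6 months, 9 months and 12 months from baseline". The abstract agrees: "Anthropometric and clinical data will be collected at five time points: baseline, 3 months, 6 months, 9 months, and 12 months from baseline".
- **HbA1c schedule.** Under the outcomes heading of Table 1, the row "Metabolic parameters (HbA1C, FBG, PBG, FCP, 2hCP, Triglyceride, Total cholesterol, HDL cholesterol, LDL cholesterol" carries dots at PS and at M12.
- **HbA1c as an outcome.** Section 2.4.1: "The primary outcome measure is the change in mean HbA1c level, measured at baseline and 3 months post-intervention". Section 2.4.3 places the primary endpoint after three months of intervention, which is M3. The five numbered secondary groups cover hypoglycaemia and side effects; C-peptide and complications; insulin dose and service use; microbiota and permeability; and quality of life. None names HbA1c.
- **Analysis.** Section 2.5 compares HbA1c between groups by ANOVA, presented as the primary outcome, with no visit given. Covariate adjustment appears only as a step after a significant difference. Its examples are sex and age, not baseline HbA1c. Section 2.5 also plans intention-to-treat analysis with multiple imputation.

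**The concern.** Nine of the twelve months after baseline are off drug. The trial's main measure is collected in that time but has no stated role there. The Introduction motivates the work partly by the hope that "combination therapy may have the potential to improve long-term blood glucose control and delay disease progression in LADA patients", and readers of the results will ask whether a difference at M3 lasts.

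As the article stands, an answer could be drawn from M6, M9 or M12, for any of three active arms against placebo. No visit is named in advance, and the values are not declared descriptive either. The pairwise adjustment in section 2.5 is not described as covering a choice among visits. What is at stake is selective emphasis in a secondary claim, using data that are already scheduled.

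**Working it through.** **1. When HbA1c is measured.** The metabolic row of Table 1 has dots only at PS and M12. The insulin injection row, which describes a continuous treatment, is marked the same way, so the dots most plausibly mark the two ends of a span. With the five visit times in section 2.1 and the abstract, this gives HbA1c at M0, M3, M6, M9 and M12. No cell marks M6 or M9, so those two are inferred. On the narrowest reading, M12 is still scheduled.

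**2. Size of the open choice.** Span reading: 3 off-drug visits × 3 active arms = 9 contrasts with placebo. Narrowest reading: 1 × 3 = 3. With full attendance, 240 × 3 = 720 of 240 × 4 = 960 post-baseline tests serve no named outcome.

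**3. The plan's own sample size.** Inputs from section 2.1.2: difference 0.44, SD 0.80, two-sided α 0.05, power 80%.
- Normal approximation: n = 2 × (1.96 + 0.8416)² × (0.80/0.44)² = 51.9, so 52 per arm.
- Two-sample t-test: 52.87, so 53 per arm, with power 0.801.
- 53/(1 − 7/60) = 60 enrolled per arm, an allowance of 11.7%.

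The stated 53 and 60 reproduce. Nothing here disputes them.

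**4. Precision of a later arm-minus-placebo difference, unadjusted.** Half-width = multiplier × 0.80 × √(2/n).
- n = 53: 0.80 × √(2/53) = 0.1554. Multiplied by 1.96 this is 0.305; by t = 1.983 (104 df) it is 0.308. About 0.31.
- n = 42 (60 × 0.70, a 30% loss that is assumed): 0.80 × √(2/42) = 0.1746. Multiplied by 1.96 this is 0.342. About 0.34.

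**5. Effect of baseline adjustment.** The gain depends on the correlation r between baseline and later HbA1c, which the article does not give. It also depends on whether the SD of 0.80 refers to a single value or to a change, which section 2.1.2 does not say. Starting from 0.308 at n = 53:

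| r (assumed) | 0.80 is SD of the value: × √(1 − r²) | 0.80 is SD of the change: × √((1 + r)/2) |
|---|---|---|
| 0.4 | 0.28 | 0.26 |
| 0.6 | 0.25 | 0.28 |
| 0.8 | 0.18 | 0.29 |

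**6. Power off drug**, unadjusted, for assumed retained effects:

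| Retained difference | n = 53 | n = 42 |
|---|---|---|
| 0.44 (all) | 80% | 70% |
| 0.33 | 56% | 46% |
| 0.22 | 29% | 24% |
| 0.11 | 11% | 10% |

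A later visit can be estimated with a useful interval. It is a weak test of a partly retained effect.

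**The case against.** The strongest reply is that this is a condensed article. Visit-level secondary time points and model details often sit in a full protocol or analysis plan that is not shown. The secondary list is introduced in words that need not be exhaustive. The HbA1c ANOVA and the abstract's HbA1c outcome carry no date, so they do not exclude later visits. All of this stands against a stronger claim. It does not supply an outcome: the numbered list goes down to emergency visits and still omits HbA1c after M3, and the stated ANOVA has no baseline term.

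Four stronger inferences are tempting, and the documents support none of them.
- **That the trial cannot make any planned statement on durability.** The article shows only that it names no off-drug HbA1c outcome.
- **That the follow-up exists to test durability.** Persistence after stopping is not a stated objective. The Introduction's remark on long-term control concerns combination therapy in general. The follow-up also serves complications, microbiota, permeability and quality of life, all scheduled at M12.
- **That later comparisons would rest on whoever still attends.** Section 2.5 plans intention-to-treat analysis with multiple imputation.
- **That follow-up has no glycaemic information.** Daily insulin dose is a listed secondary outcome, with logs to M12, though without a named time.

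The insulin point also limits the remedy. Section 2.3 has insulin adjusted on the glucose readings before each visit, which would tend to draw HbA1c together across arms. Similar HbA1c at M12 would not by itself show that a benefit was lost, so HbA1c and insulin dose must be read together.

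**Conclusion.** The point holds as a gap between the article's schedule and its outcome list. HbA1c is collected off drug to M12, is named as an outcome only for M0 to M3, and has one undated ANOVA without baseline. A persistence claim would be picked from up to nine contrasts after the data are seen. That count rests on reading the Table 1 dots as a span; on the narrowest reading it is three.

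The M3 primary inference, the 53 and 60 per arm, and the handling of missing data are untouched. This is a worthwhile, cheap improvement and not a fault in the main result. The precision figures rest on the plan's SD of 0.80 holding at later visits, and the lower n rests on an assumed 30% loss.

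**What to change.** 1. **Section 2.4.1.** Add as a secondary outcome the change in HbA1c from M0 to M6, M9 and M12. Name one main visit in advance, for example M12, and report daily insulin dose at the same visits beside it. Writing M3 in the primary outcome would also remove a possible reading of its time as three months after the drugs stop.
2. **Section 2.5.** Replace the HbA1c ANOVA with one repeated-measures mixed model of HbA1c at M3, M6, M9 and M12, with arm by visit, baseline HbA1c by visit, and the two stratification factors (BMI and chronic complications). Report arm minus placebo with a 95% CI at each visit. M3 stays the primary time, and the intention-to-treat population and multiple imputation stay as planned.
3. **Labelling.** State that the M6, M9 and M12 estimates are secondary.
4. **Table 1.** Mark HbA1c in each visit column so that M6 and M9 need not be inferred.

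The cost is one outcome line, one model paragraph and a table edit, settled before unblinding. On the span reading, no visit, test or patient is added. The price is that the later estimates are imprecise and must be presented as such.
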